### Ethical issues

#### Ethics committee approval

The trial has been approved by the Ethics Committee of the CHU de Québec-Université Laval in Québec, Canada and of all 40 participating hospitals (MP-20-2016-2718; MP-20-2017-3220). The PRISMA trial is registered on the ISRCTN registry under the number ISRCTN15346559 (http://www.isrctn.com/). The results of the trial will be reported according to the CONSORT Statement (SPIRIT Checklist, Additional file 1).

#### Information and consent forms

The participating hospitals are included on the basis of an informed consent form signed by the head of obstetrics. The informed consent form specifies that: (1) the site can withdraw from the program at any time; (2) the data collection will continue until the end of the trial, even if a site withdraw from the project; and 93) that the PRISMA program will be offered to control group hospitals at the end of the trial if the intervention is proven effective. Collection of clinical data from medical records is authorized by the director of professional services in each participating hospital and does not require patient consent. During the intervention period, the involvement of patients will be sought with the use of the decision analysis tool (DAT) and for the LUS thickness measurement. The DAT includes an implied consent which states that filling it and returning it to their physician represent a women’s consent to use the DAT. The authorisation for an additional ultrasound measurement (LUS thickness) will be obtained by a written information and consent form.

#### Interim analyses and stopping rules

An independent Data Safety and Monitoring Board (DSMB) has been established, made up of three international experts in epidemiology and biostatistics, reproductive health research, and obstetrics and gynaecology. It will be responsible for ensuring the safety of the trial and for monitoring the progress of the research according to the protocol. Serious adverse events (maternal and perinatal death, perinatal asphyxia, hemostatic, hysterectomy, uterine rupture) will be monitored annually during the intervention by the DSMB, blinded, for all patients in the study. To assess the effectiveness of the program at the end of the first year of the intervention period, an intermediate analysis will be planned using Peto criteria (*α* = 0.001), which ensure that a total type-I risk of error, for the final analysis, of 0.05. The DSMB may decide to stop the trial for the following reasons: detection of adverse events, poor data quality, low levels of implementation, high contamination in the control group, fraud, and new information that would rule the trial unnecessary, futile, or unethical.

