### Statistical analysis plan

#### Sample size and power calculation

The sample size was calculated to maximize statistical power while minimizing the number of clusters [64]. Sample size calculations were based on a cluster RCT design [65], stratified by level of care (community, regional or tertiary care hospitals), to detect a relative reduction of 25% in major perinatal morbidity in hospitals of the intervention group compared with those of the control group. To account for clustering by hospital, we assumed an intraclass correlation coefficient of 0.001, estimated from the QUARISMA Trial data, representing 70% of deliveries in Quebec in 2010–2011 [64]. We calculated that we would have to enroll 40 hospitals in the study, with an expected total of 7360 women with one prior cesarean delivery per year (22,080 women for the 1-year baseline period and the 2-year intervention period), to achieve a power of 80% to detect a 25% relative reduction with the intervention in the major perinatal morbidity rate, assuming a baseline rate of 4.5% for the three strata, at a two-sided alpha significance level of 0.05 [64, 66].

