#### Statistical analysis

For reducing contamination bias, hospitals are the units of randomization and patients are the units of analysis [64, 67]. In the primary intention-to-treat analyses, we will assess the effect of the intervention on the rate of major perinatal morbidity using the multivariable generalized-estimating-equations extension of logistic regression, with an exchangeable covariance matrix, to account for the clustering of women within hospitals [68]. Changes in the risk of major perinatal morbidity in the two study groups between the 1-year baseline (pre-intervention) period and the 2-year intervention period will be compared with the use of an adjusted odds ratio (with 95% confidence intervals) for the interaction between group (intervention vs. control) and time period (intervention vs. baseline) [64, 65]. The adjusted odds ratio for interaction will be estimated with the use of data on women who were delivered during the baseline period or the intervention period and measures the intervention effect with the difference-in-differences approach [69, 70], which is adapted for generalized-estimating equation analyses of clustered binary outcomes [65]. In each group, the change over time, from the baseline to the intervention period, will be measured by the respective odds ratio, i.e. the exponent of the difference between log odds of cesarean delivery in intervention versus baseline periods. Then, additional change over time in the intervention group, relative to the concurrent change in the control group, will be estimated by the difference between group-specific differences. The exponent of the resulting difference-in-differences in log odds provides the adjusted odds ratio, with 95% CIs, for the interaction between group (intervention vs. control) and time (intervention vs. baseline), which will be used as the main measure of the intervention effect [64, 69, 70]. Two-tailed *P* values of less than 0.05 will be considered to indicate statistical significance.

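### The claimed total type-I error of 0.05 holds only if the GEE test is valid with 40 hospitals; in its usual uncorrected form the total is about 6% to 7%, and up to about 8% with very unequal hospitals

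*Protocol article*

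**What the plan says.** All references are to the protocol article.

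- *Interim analyses and stopping rules*: the efficacy look is introduced with "To assess the effectiveness of the program at the end of the first year of the intervention period", then "an intermediate analysis will be planned using Peto criteria" at α = 0.001, "which ensure that a total type-I risk of error, for the final analysis, of 0.05".
- *Statistical analysis*: the test is the "multivariable generalized-estimating-equations extension of logistic regression, with an exchangeable covariance matrix, to account for the clustering of women within hospitals". The group-by-period odds ratio with its 95% CI is the quantity "which will be used as the main measure of the intervention effect". For two-tailed P, "values of less than 0.05 will be considered to indicate statistical significance", so the final level is not lowered for the interim look.
- *Sample size and power calculation*: 40 hospitals, 7360 women per year, a 4.5% event rate and an ICC of 0.001, "at a two-sided alpha significance level of 0.05".
- *Potential limitations of the trial*: delivery numbers differ between hospitals. No measure of that spread is given.

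No section says whether the standard error is empirical or model-based, whether it is corrected for the number of clusters, or whether P values come from a z, t or score test. The analysis section does guard against standard errors that are too small, by requiring P below 0.001, but only where the GEE fails to converge and ordinary logistic regression replaces it.

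**The concern.** A stopping rule allocates error between looks. It keeps the total at 0.05 only if each P value is correct. The ordinary GEE sandwich standard error is a large-sample estimate in the number of clusters, which here is 20 per arm. With so few it tends to be too small, more so when cluster sizes differ, and the normal reference is too narrow. The relative error is largest in the far tail, where the 0.001 boundary lies.

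The primary P value, its 95% CI and the one-year efficacy look all depend on this standard error. If it is too small, the interval covers less than 95%. A primary result with nominal P of about 0.03 to 0.05 could then be called significant when a valid clustered test would not agree.

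**Working it through.** **1. Inputs.** From the article: 40 hospitals (20 per arm); 7360 / 40 = 184 women per hospital per year; rate 4.5%; ICC 0.001; one baseline year and two intervention years; interim level 0.001 and final level 0.05, two-sided. Assumed, because not given: CV of hospital size from 0 to 1.0, and correlation of hospital effects between periods (various values; 0.8 in the table below).

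**2. The plan's own figure.** With b women at baseline and y per intervention year, the variance of the difference-in-differences is proportional to 1/b + 1/y at the interim and 1/b + 1/(2y) at the end. With b = y, the information fraction is 1.5 / 2 = 0.75, and the correlation between looks is √0.75 = 0.87. The bivariate-normal probability of |Z₁| > 3.29 or |Z₂| > 1.96 is 0.05002. At an information fraction of 0.5 it is 0.0502. The stated 0.05 is reproduced.

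**3. The reference distribution alone.** If the statistic behaves like t with 38 degrees of freedom but is read against the normal, P(|t₃₈| > 1.96) = 5.7% and P(|t₃₈| > 3.29) = 0.22%. This excess comes before any downward bias in the sandwich standard error.

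**4. Simulation under no effect.** Exchangeable logistic GEE with group, period and their interaction; interim on baseline plus year 1, final on baseline plus two years; 30,000 trials per row; ICC 0.001.

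| Size CV | Sandwich z: interim | final | either look | Model-based z: either | Score test: either |
|---|---|---|---|---|---|
| 0 | 0.31% | 6.38% | 6.40% | 5.38% | 5.17% |
| 0.6 | 0.44% | 7.14% | 7.17% | 5.74% | 5.32% |
| 0.8 | 0.41% | 7.49% | 7.52% | 5.89% | 5.47% |
| 1.0 | 0.54% | 7.62% | 7.68% | 5.81% | 5.14% |

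Further runs, with and without level-of-care terms and with other between-period correlations, gave these results for the sandwich z-test:

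- Total: 6.2% to 6.7% with equal or near-equal sizes, and 7.3% to 8.1% at CV 1.0.
- Interim crossing: 0.24% to 0.31% with equal sizes, and up to 0.58% at CV 1.0, against a nominal 0.1%.
- ICC 0.005 (CV 0.6 and 0.8): total 7.0% to 7.7%.

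The lowest total, 0.0622 on 14,000 trials, has Monte Carlo standard error √(0.0622 × 0.9378 / 14,000) = 0.0020. It therefore lies about 6 standard errors above 0.05.

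In the last row of the table the interim look adds 7.68 − 7.62 = 0.06 percentage points. The rest is the final test.

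**5. Partial remedies.** The sandwich with t(38) gives totals of 5.5% to 7.0% and interim crossing of 0.12% to 0.31%. The model-based standard error with z gives 5.4% to 5.9% and about 0.15%.

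The model-based excess depends on the assumed between-period correlation of 0.8. That leaves 0.001 × 0.2 = 0.0002 of period-specific correlation, which an exchangeable matrix does not represent. With equal sizes the variance is understated by a factor 1 + 183 × 0.0002 = 1.037, and 2{1 − Φ(1.96/√1.037)} = 5.4%. At CV 1.0 the effective cluster size is 184 × 2 = 368, the factor is 1 + 367 × 0.0002 = 1.073, and the result is 5.9%. These match the simulated 5.38% and 5.81%.

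**6. Small-sample methods.** A Mancl-DeRouen-type variance with t(38) gives totals of 4.1% to 4.9% and interim crossing of about 0.1% (0.05% to 0.15%). The score test gives 5.1% to 5.5% and 0.03% to 0.06%.

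**The case against.** The strongest reply is that the quoted sentence describes how the Peto rule spends alpha, and on that it is right. A reader might infer that 0.001 followed by an unreduced 0.05 overspends. Step 2 shows that it does not.

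The second reply is that the article does not choose the uncorrected sandwich z-test. It is silent, and the variance estimator is often left to a full protocol or SAP, neither of which is shown. This also stands: one may not infer that the trial will run at 6% to 8%. Nothing in the article conflicts with a corrected variance.

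Third, the upper figures (about 8%, and nearly six times 0.001) need a hospital-size CV near 1.0, which the article does not give. The simulations adjust at most for level of care, not for the planned maternal and perinatal covariates. Crossing 0.001 is also not an automatic stop, since the monitoring board retains discretion.

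What remains is that the article goes beyond silence: it asserts that 0.05 is ensured. An odds ratio from a GEE coefficient with a 95% CI is most naturally read as Wald inference, and the usual sandwich version misses 0.05 even with equal hospitals. The article treats understated standard errors as a matter to settle here, but only for non-convergence.

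**Conclusion.** The point holds in conditional form. The Peto split is correct; the assurance of 0.05 depends on a test that is valid with 40 clusters, and the article does not secure one. With the usual uncorrected sandwich z-test:

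- the total is about 6.2% to 6.7% with equal hospitals, an excess of 1.2 to 1.7 percentage points that needs no assumption about unequal sizes;
- it reaches about 8% only if the size CV is near 1.0;
- nearly all the excess belongs to the final analysis;
- the interim boundary is crossed roughly 2.5 to 3 times too often with equal sizes, and more often with very unequal ones.

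A t(38) reference alone reduces the excess without removing it. So does a model-based standard error in these runs, though that residual rests on the assumed between-period correlation. If an unshown SAP already names a small-sample method, a cross-reference settles the point.

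**What to change.** In *Statistical analysis*, state that the P value and 95% CI for the group-by-period odds ratio use a GEE method valid for this number of hospitals. One option is a Mancl-DeRouen-type corrected variance with a t reference whose degrees of freedom are based on the number of hospitals. The simulations used 40 − 2 = 38; the plan should state its own count if hospital-level covariates are included. A comparable method such as a score test would also serve. In *Interim analyses and stopping rules*, say that both looks use this method and tie the 0.05 statement to it. Keep 0.001 and 0.05.

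No new data are needed. The cost is slightly wider intervals, a small loss of nominal power and, with the corrected variance, mild conservatism (total about 4.1% to 4.9%). The score test would be slightly above 0.05 in total (5.1% to 5.5%) and stricter than 0.001 at the interim.

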### Sponsor and project administration

The project was approved by the Canadian Institutes of Health Research (CIHR) and funded in July 2015. The trial begun in April 2016. The funds are managed by the Université Laval. The multidisciplinary PRISMA research group is composed of researchers and physicians from Canada, United States and France with an international expertise in maternal and perinatal health, VBAC, clinical research, RCTs, biostatistics, improvement of quality of care and assessment of health care programs. The PRISMA intervention program is coordinated by a group of experts in maternal health and VBAC, in collaboration with the Society of Obstetricians and Gynaecologists of Canada (SOGC), the Ministère de la santé et des Services Sociaux du Québec (MSSSQ), the Association des Obstétriciens Gynécologues du Québec (AOGQ), the Association des Omnipraticiens en Périnatalité du Québec (AOPQ), and the Canadian Association of Perinatal and Women’s Health Nurses (CAPWHN). The management of the program implementation in hospitals of the intervention group and the conduct of mid-intervention audits will be carried out by the administrative coordinator of the trial. The data management and quality control are assumed by the scientific coordinator, who is also responsible for sending data to the DSMB for annual assessment of the safety of the trial and compliance with the protocol and timeline. The data collection and the intervention are two independent processes. A cross-disciplinary Steering Committee, with extensive international expertise in RCT, VBAC, quality of care improvement and health care program assessment, meets at least every 3 months to coordinate the trial, taking into account DSMB recommendations.

## Discussion

The PRISMA trial is a phase III cluster randomized controlled trial to assess the effectiveness of a multifaceted intervention aiming to reduce severe perinatal morbidity in women with one previous cesarean delivery. The PRISMA Program is designed to facilitate: 1) women’s decision-making process, using a decision analysis tool (DAT); 2) an estimate of uterine rupture risk during TOL using ultrasound evaluation of low-uterine segment thickness; 3) an estimate of chance of TOL success, using a validated prediction tool; and 4) the implementation of best practices for intrapartum management.

The DAT will be available in each intervention hospital in the clinic waiting rooms and distributed by the treating physician early during the pregnancy to help women make an enlightened choice. This tool will be also discussed with the physician during the next appointment. An onsite professional training program from the SOGC including decisional algorithms about selection of women for a TOL, chance of VBAC success, optimal management of delivery and labor dystocia among women with one prior cesarean delivery, is also planned in each intervention hospital. This professional training will be planned several times in each hospital in order to be able to train a high number of health professionals (obstetricians and gynaecologist, family physician, nurses, midwives). Finally, several onsite ultrasound training are planned in each intervention hospital, during the 5-month implementation period, in order to train ultrasound health professionals to assess the risk of uterine rupture at 35 weeks (LUS technic) among women with one prior cesarean delivery.

An important challenge relies in the implementation of the program, which may differ in different hospitals. In this Trial, a high level of implementation will be ensured by the support of local partners and healthcare professionals identified in intervention hospitals, by continuous internal assessments for compliance, by an annual site monitoring visit or more if required, and by a centralized platform in Québec allowing an external validation of each LUS thickness measures. This real time validation will ensure a constant follow up with participating physicians.

The PRIMSA Program aims to provide the right intervention for the right woman at the right time, and will contribute to reduce the perinatal morbidity among women with a prior cesarean delivery. This trial will provide a high level of evidence regarding the choice of the optimal mode of delivery, as well as the management of delivery in women with a prior cesarean.

### Trial status

At the time of submission, participating hospital have been enrolled, randomized and patient recruitment begun in one hospital.
